### 2.5. Statistical Analysis Plan

Continuous variables will be presented as the mean and standard deviation or as the median and interquartile range. Normality in the distribution will be tested with the Shapiro–Wilk test. Categorical variables will be summarized in terms of absolute and relative frequencies.

To determine whether the new diagnostic protocol can improve the ability to detect hydrocephalus as well as the timeliness of the diagnosis and the clinical rehabilitative outcomes, the historical and prospective cohorts will be compared with respect to the following: hydrocephalus diagnosis detection rate, time from admission to diagnosis, LOS, incidence of clinical complications, and DRS and LCF scores at discharge (T3). In the subgroup of patients with low responsiveness, the clinical rehabilitative outcome at discharge will be measured using the CRS-R score. Continuous variables will be compared using Student’s *t* test, when normally distributed, or the Mann–Whitney U test otherwise. Categorical variables will be compared using Pearson’s χ^2^ test or Fisher’s exact test as appropriate. The same tests will be used to compare patients with and patients without a diagnosis of hydrocephalus belonging to the prospective cohort, in terms of the following: clinical rehabilitative outcome at T3 and T4 measured using the DRS, LCF and CRS-R scale scores; evolution from T0 to T4 of quality of life measured using the QOLIBRI-OS; neuroradiological characteristics at T1 and T3 or T4 measured using Evan’s index, callosal angle and volumetric analysis. To complement the information provided by the statistical tests, differences between groups will be quantified in terms of the effect size (standardized mean differences for continuous variables; difference between proportions or odds ratios for categorical variables) and its standard error. In addition, outcome variables will be compared between the historical and prospective cohorts, adjusting for demographic and clinical confounders in multivariable regression analyses. Confounders to be included in the models are those significantly associated with the outcomes and significantly different between the two cohorts. 

Two-sided tests will be carried out, and the statistical significance level will be set at 0.05. All analyses will be performed with Stata version 17.0 (Stata Corp., College Station, TX, USA).

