In a previous study, a 13.2% incidence of secondary hydrocephalus was reported among 621 hospitalized patients with sABIs [7]. The diagnosis was based on the previously indicated combination of clinical and radiological criteria, but we hypothesized that cases may have been under-detected, especially in patients with disorders of consciousness and/or many confounding comorbidities, due to the absence of a reference standard. In addition, the study showed that after VPS placement, most patients had a clinical improvement and none worsened; however, a delay in surgical treatment resulted in a longer hospitalization and was associated with worse outcomes. That study underscored the need for a more standardized approach to the diagnosis of secondary hydrocephalus, with a better timing in the evaluation of patients with sABIs during inpatient rehabilitation in order to improve the selection of those who may benefit most from surgical treatment [17].

In this position paper, we describe a diagnostic protocol for hydrocephalus that integrates clinical, functional, biochemical and neuroradiological assessments. The aims of the protocol are as follows:To increase the hydrocephalus detection rate;To reduce the time for hydrocephalus diagnosis/surgical treatment;To improve the clinical rehabilitative outcomes at discharge;To reduce the overall length of hospitalization (LOS) and the occurrence of complications in patients diagnosed with and treated for hydrocephalus.

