### 2.4. Clinical Diagnostic Protocol and Study Assessments

A multidisciplinary team of physiatrists, neuroradiologists, neuropsychologists and neurosurgeons designed the new protocol for the diagnosis of suspected secondary hydrocephalus and its confirmation, based on the best recommendations in the literature [18,19,20]. The timing and procedures included in the diagnostic protocol are shown in Figure 1. 

Within 7 days (week 1) of hospital admission, i.e., at baseline (T0), patients with sABIs will undergo the following evaluations:Socio-demographic and anamnestic data collection;Neurological examination;Clinical and functional assessment;Neuroradiological exam (brain CT);Neurophysiological exams.

Clinical and functional assessments will be performed at weeks 3 and 5, before the multidisciplinary team meeting. An additional CT scan and a brain MRI will be performed after 30 days (week 5) from admission (T1) to assess the presence of ventricular dilation signs. The first multidisciplinary team meeting will be held about 40 days (week 6) after admission, with the aim of evaluating the results of the neurological examination, neuroradiological exams, and clinical and functional assessments. The multidisciplinary team will identify patients with suspected hydrocephalus based on the presence of at least one of the following criteria:Neuroradiological criteria: increase in ventricular dimensions with supratentorial and subtentorial ventricular dilation, or both; sulcal reduction at the convexity; Evan’s index increase; callosal thickness reduction; callosal angle increase; presence of periventricular white matter changes; presence of aqueductal flow void.Clinical criteria: worsening or stopping of clinical recovery as assessed based on clinical scales and functional tests.

Patients with “suspected hydrocephalus” will undergo further evaluations to confirm the diagnosis, specifically:High-volume tap test (TT);CSF examination;Clinical and functional assessments 1, 3 and 7 days after TT;Multidisciplinary team evaluation 7 days after TT.

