## 3. Expected Results

We expect to find, in the prospective cohort as compared to the historical cohort, an increase in the proportion of diagnosed cases, a significant reduction in the time elapsed between admission and diagnosis and, consequently, a shortened time to surgery as well as a shortened overall LOS.

We assume that early diagnosis and treatment may result in a decreased incidence of clinical complications and may improve the rehabilitative outcomes at discharge among patients with hydrocephalus, especially in the subgroup with low responsiveness.

In addition, we expect to obtain useful information about the diagnostic and prognostic value of the neuroradiological characteristics.

Lastly, from the comparison of patients with and without hydrocephalus in the prospective cohort, we expect to observe that the adoption of an objective and timely protocol for the diagnosis and treatment will allow patients with hydrocephalus to obtain similar clinical rehabilitative outcomes and perceived quality of life to those who do not develop this complication.

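### Time to diagnosis is compared by tests that can use only diagnosed patients, a group the new protocol is meant to enlarge, so the timing aim can be misjudged in either direction; time to surgery, also an aim, is not among the listed comparisons

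*Protocol article*

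**What the plan says.** The second aim in section 1 is "To reduce the time for hydrocephalus diagnosis/surgical treatment". Section 3 expects quicker diagnosis and, as a consequence, "a shortened time to surgery as well as a shortened overall LOS". It also expects a larger share of patients to be diagnosed.

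Section 2.5 lists what will be compared between the historical and prospective cohorts: "hydrocephalus diagnosis detection rate, time from admission to diagnosis, LOS, incidence of clinical complications, and DRS and LCF scores at discharge (T3". Time to surgery is not in that list. On method it says: "Continuous variables will be compared using Student’s *t* test, when normally distributed, or the Mann–Whitney U test otherwise". A further analysis compares outcomes while "adjusting for demographic and clinical confounders in multivariable regression analyses"; the type of regression is not given. No censoring, time-to-event method or competing event is mentioned, and no analysis set is stated for time to diagnosis.

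**The concern.** A patient who is never diagnosed has no time to diagnosis. A t test or Mann–Whitney test must leave that patient out, so the comparison runs between two groups that are each selected by being diagnosed. Being diagnosed is the outcome that the new protocol is designed to change. Cases that would have been missed in 2015–2019 enter only the prospective group, and their diagnosis times are mixed with those of cases that would have been found anyway.

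The added cases need not resemble the others. Section 1 suspects that missed cases were mainly patients with disorders of consciousness or many comorbidities, who might be diagnosed late. Section 4 expects structured imaging to pick up patients with no clinical suspicion, who might be diagnosed early. The difference in mean or median time therefore combines a change in timing with a change in who is counted.

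Separately, surgery is half of the timing aim, yet the explicit list of comparisons does not cover it.

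**Working it through.** **The plan's own figures.** Section 2.2: 2 years × 50–60 patients = 100–120 patients; 20% of these = 20–24 cases. The stated count of at least 20 cases is reproduced.

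**Share of added cases.** Section 1 reports 13.2% in the previous study of 621 patients; section 2.2 expects about 20%. Assume that 13.2% applies to the historical cohort and that the new protocol finds all such cases plus others. Then (20 − 13.2)/20 = 6.8/20 = 34% of prospective cases are added ones, about 7 to 8 of the 20–24.

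**Mean among diagnosed patients.** The documents give no diagnosis times, so all times here are assumptions. With historical mean m, a true gain of g days for existing cases, and added cases averaging day x:

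prospective mean = [13.2 × (m − g) + 6.8 × x] / 20

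- m = 70, g = 10, x = 120: (13.2 × 60 + 6.8 × 120)/20 = (792 + 816)/20 = 80.4 days, against 70. It looks 10.4 days later although every existing case was found 10 days sooner.
- m = 70, g = 0, x = 50: (13.2 × 70 + 6.8 × 50)/20 = (924 + 340)/20 = 63.2 days, against 70. It looks 6.8 days earlier although no existing case was found sooner.

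**Break-even.** The prospective mean exceeds m when x > m + g × 13.2/6.8. For m = 70 and g = 10 this is (1400 − 792)/6.8 = 89.4 days. For true gains of 5, 20 and 30 days it is 79.7, 108.8 and 128.2 days. The larger the true gain, the later the added cases must be to hide it.

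**The same first example in all patients.** If every case falls exactly on its assumed day, the percentages diagnosed (historical v prospective) are 0 v 13.2 by day 65, 13.2 v 13.2 by day 90, and 13.2 v 20 by day 150. The prospective cohort is never behind. Mean time undiagnosed up to day 180 is (13.2 × 70 + 86.8 × 180)/100 = 165.5 days v (792 + 816 + 80 × 180)/100 = 160.1 days, so 5.4 days shorter.

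**Simulation of the planned test.** There were 3000 runs of a two-sided Mann–Whitney test at 0.05. Assumed: 275 historical patients (five years at 50–60 a year gives 250–300), 110 prospective patients, historical mean 80 days, SD 30 days.

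| True gain, existing cases | Mean day, added cases | Mean difference among diagnosed | Runs with later prospective mean | Significant later | Significant earlier |
|---|---|---|---|---|---|
| 10 days | 120 | +6.8 days | 76% | 9% | 0.6% |
| 10 days | 150 | +17.0 days | 92.5% | 22% | 0.1% |
| 0 days | 50 | −9.8 days | 13% | 0.1% | 20% |
| 20 days | 60 | −19.5 days | 0.8% | 0% | 64% |

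In the last row the added cases have the same mean time as the existing prospective cases (80 − 20 = 60), and the true gain is recovered. The distortion depends on how far the two groups differ.

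**Time to surgery.** The section 1 aim and the section 3 expectation both name it; the section 2.5 list does not. Section 2.4 adds that some confirmed cases will not be operated on because of severity or refusal by the family. A comparison among operated patients only would therefore have the same selection problem.

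**The case against.** The plan does not say that only diagnosed patients are analysed, and the regression type is open, so a time-to-event model is not excluded for the adjusted analysis. That is fair, but the unadjusted tests are named and cannot use a patient without a date.

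Nothing in the documents makes day 120 typical. All patients have imaging after 30 days, and section 2.4 states "The first multidisciplinary team meeting will be held about 40 days (week 6) after admission", so the added cases may well be early; a significant wrong-way result arose in only 9% of runs in the nearest scenario. This stands against any claim that the result will reverse. It does not rescue the comparison, because early added cases bias it in the favourable direction.

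The detection rate is reported alongside, so a change in case mix would be visible. It would be visible but not corrected.

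Two stronger readings are tempting. One is that the schedule (review at about day 40, tap test, team review 7 days later, hence about day 47) biases the comparison. If the schedule delays diagnosis, that is a real effect of the protocol and should show. Section 2.4 also does not fix which date counts as confirmation, since assessments take place 1, 3 and 7 days after the tap test. The other is that deaths counted as short stays reverse the result. The documents do not mention in-hospital death, and its handling may sit in a fuller plan. LOS is also a separate outcome and cannot reverse time to diagnosis. On assumed values (survivor stays of 120 v 110 days, deaths at day 40), mortality of 10% v 5% leaves the LOS gain standing at 112.0 v 106.5 days; it takes about 15% v 3% to erase it (108.0 v 107.9).

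**Conclusion.** The concern holds for time to diagnosis and for the missing time to surgery. Followed as written, the unadjusted comparison for the second aim rests on a group whose membership the protocol changes, and about a third of prospective cases (34%) would have no historical counterpart. That share assumes that the previous study's 13.2% applies to the historical cohort and that the expected 20% is reached.

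The direction of the bias is not known. With an assumed move from day 70 to day 60, a true gain looks like a delay once the added cases average beyond about day 89, and early added cases produce or inflate a gain. The sizes rest on assumed times; the mechanism does not.

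The omission of time to surgery is a plain mismatch between the aims and expected results on one side and the listed comparisons on the other. A reader might also infer that the result must reverse, that the review schedule is itself a bias, or that deaths within LOS undermine the timing result. The documents support none of these.

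**What to change.** - In all patients of both cohorts, counted from admission, estimate the cumulative incidence of diagnosis and of shunt surgery, with death or discharge without the event as competing events. Compare the cohorts at fixed times named in advance, for example 3 and 6 months.
- Add time to surgery to the outcome list in section 2.5.
- Keep time to diagnosis among diagnosed patients as a descriptive figure, without a test of the timing aim.
- Keep any covariate adjustment sparse, since about 20 prospective cases will not carry a rich hazard model.
- Optionally, analyse LOS as time to live discharge as a sensitivity analysis.

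The cumulative incidence curves show how many patients have been diagnosed or operated on by each date. They do not show that the same cases are found sooner, and the report should say so.

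The cost is a change of wording and a little more analysis, with no change to care or recruitment. The main drawback is reliance on event dates in the historical records: section 4 warns that the historical cohort may lack complete information, so completeness of admission, diagnosis, surgery, discharge and death dates should be checked and reported.

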Diagnosis confirmation derives mainly from the improvement of the patient’s clinical/neurological condition after CSF TT, measured as an improvement in the score of the clinical scales before and after the test or as an improvement in the performances in the functional tests. The main clinical rating scale is the Disability Rating Scale (DRS). The Levels of Cognitive Functioning (LCF) scale corroborates the DRS result. The Coma Recovery Scale Revised (CRS-R) will be used for patients with low responsiveness or severe disturbance of consciousness. 

Specifically, the diagnosis will be confirmed when at least one of the following changes occurs after TT:
Decrease in the DRS score;Increase in the LCF score;Increase in one of the CRS-R scale’s items that identify a minimally conscious state or emergence from a minimally conscious state;Improvement in one of the functional tests (TUG, 10 mWT, POMA).

Patients with a confirmed diagnosis will receive an indication of surgical treatment with shunt placement.

Both the severity of the clinical condition and the consent being denied by family are reasons that preclude the intervention, even in the case of a diagnosis confirmation.

During the hospital stay, the multidisciplinary team will evaluate the presence of suspected hydrocephalus in patients with no previous diagnosis. Patients with suspected hydrocephalus will be treated following the clinical diagnostic protocol just described.

The study flow is described in Figure 2. 

All patients will undergo a reassessment of all clinical and functional scales, neurological and neurophysiological examinations and a brain CT scan at three time points: 1 month after surgery for those treated with a VPS/VAS or at 3 months from hospital admission for patients without a diagnosis of hydrocephalus or who did not receive a VPS/VAS placement (T2); at discharge (T3); and 1 year after hospitalization (T4). All the patients will undergo a brain MRI at T3 and, if prescribed by the multidisciplinary team, at T4. 

Table 1 summarizes the clinical parameters, clinical measurement scales, functional tests, and neurophysiological and neuroradiological exams included in the study.

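### The comparison of patients with and without hydrocephalus has no landmark, although diagnosis is not scheduled to be confirmed before about day 47, so early discharges may distort it to an unknown extent

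*Protocol article*

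**What the plan says.** Section 2.1 excludes patients whose hydrocephalus was diagnosed or treated before admission, and those with acute hydrocephalus. Nobody therefore enters the prospective cohort already in the diagnosed group.

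Section 2.4 gives the timetable. Suspicion is first judged by the team: "The first multidisciplinary team meeting will be held about 40 days (week 6) after admission". Suspected cases then have a tap test, followed by "Clinical and functional assessments 1, 3 and 7 days after TT" and "Multidisciplinary team evaluation 7 days after TT". On the criterion, "the diagnosis will be confirmed when at least one of the following changes occurs after TT". Diagnosis can also come later: "During the hospital stay, the multidisciplinary team will evaluate the presence of suspected hydrocephalus in patients with no previous diagnosis". No timing is given for these later reviews.

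Section 2.5 sets the comparison: "The same tests will be used to compare patients with and patients without a diagnosis of hydrocephalus belonging to the prospective cohort". The tests are the t test or Mann–Whitney test and the chi-squared or Fisher test. The outcomes include "clinical rehabilitative outcome at T3 and T4 measured using the DRS, LCF and CRS-R scale scores", where T3 is discharge and T4 is one year. Multivariable adjustment is stated only for the historical-versus-prospective comparison.

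Section 3 says what the authors expect from this comparison, namely that the protocol "will allow patients with hydrocephalus to obtain similar clinical rehabilitative outcomes and perceived quality of life to those who do not develop this complication".

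**The concern.** The groups are defined by something that happens well after baseline, and a patient must stay in hospital long enough for it to happen. Every diagnosed patient has, by the timetable, stayed about seven weeks. The undiagnosed group has no such requirement. This is guarantee-time (immortal-time) selection.

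It matters because length of stay plausibly tracks recovery, and recovery is the outcome. A patient who improves quickly and goes home in week 4 has a good discharge score and no diagnosis. If such patients sit in the undiagnosed group, that group looks better than the patients who stayed as long as the diagnosed ones. A gap can then appear even if hydrocephalus and its treatment make no difference. The error works against the authors' own expectation of similar outcomes, and any one-year scores from these patients carry the same selection.

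**Working it through.** **1. The plan's own count.** Section 2.2 expects 50–60 patients a year for two years, about 20% with hydrocephalus. 2 × 50 = 100 and 2 × 60 = 120; 0.20 × 100 = 20 and 0.20 × 120 = 24. This reproduces the stated 100–120 patients and at least 20 cases. The groups are therefore about 20 versus 80, or 24 versus 96.

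**2. Earliest scheduled confirmation.** Day 40 (meeting) + 7 days (tap test to team evaluation) = about day 47, if the tap test is done on the day of the meeting. Any wait for the test moves this later.

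**3. Bias from early discharges.** Let f be the share of the undiagnosed group discharged before day 47, and g the amount, in SD, by which their mean score is better than that of patients who stayed. Suppose there is no true difference among stayers. The undiagnosed mean is then (1 − f) × stayers' mean + f × (stayers' mean improved by g), so the spurious difference is f × g.

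The documents give neither f nor g. Assumed ranges: f = 5–30%, g = 0.5–1.0 SD.

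Standard error of the standardized difference = √(1/n₁ + 1/n₂):
- 20 vs 80: √(0.0500 + 0.0125) = 0.25 SD
- 24 vs 96: √(0.0417 + 0.0104) = 0.228 SD

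Probability of a false two-sided rejection at 0.05, by normal approximation: 1 − Φ(1.96 − bias/SE) + Φ(−1.96 − bias/SE).

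| f | g (SD) | bias (SD) | false rejection, 20 vs 80 | false rejection, 24 vs 96 |
|---|---|---|---|---|
| 5% | 0.5 | 0.025 | 5.1% | 5.1% |
| 10% | 0.5 | 0.05 | 5.5% | 5.6% |
| 10% | 1.0 | 0.10 | 6.9% | 7.2% |
| 20% | 0.5 | 0.10 | 6.9% | 7.2% |
| 20% | 1.0 | 0.20 | 12.6% | 14.2% |
| 30% | 0.5 | 0.15 | 9.2% | 10.1% |
| 30% | 1.0 | 0.30 | 22.4% | 26.0% |

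**4. Cross-check with a different model.** Let stay and outcome be jointly normal with correlation r. Let a share p of the whole cohort, the shortest stayers, leave before day 47, and let 20% of all patients be diagnosed at random among those who remain. The diagnosed mean is r × φ(q)/(1 − p), where q is the p-quantile. The undiagnosed mean is −0.2/0.8 = −0.25 times that. The spurious difference is therefore 1.25 × r × φ(q)/(1 − p).

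| p | r = 0.3 | r = 0.5 |
|---|---|---|
| 2% | 0.02 SD | 0.03 SD |
| 5% | 0.04 SD | 0.07 SD |
| 10% | 0.07 SD | 0.12 SD |
| 20% | 0.13 SD | 0.22 SD |
| 30% | 0.19 SD | 0.31 SD |

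Example: p = 0.2 gives φ(0.842) = 0.280; 1.25 × 0.3 × 0.280/0.8 = 0.13. The values of r are also assumed. The two models agree on the order of size.

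**5. Effect of a landmark at about day 47.** In both models the spurious difference falls to zero by construction, because diagnosis is unrelated to stay among those who remain. For f = 5–30% the undiagnosed group falls from 80 to 76–56, or from 96 to 91–67. The diagnosed group stays at 20–24.

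**The case against.** Five points can be made against this.

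- **No classification rule is stated.** The article does not say how a patient who leaves before the work-up is grouped. Figure 2, the study flow chart, was not available to this check, and a condensed article may leave such handling to a fuller document. This stands in part: that early leavers count as undiagnosed is the natural reading of section 2.5, not a written rule. But section 2.5 does specify the groups, outcomes and tests, and the comparison as specified does not separate patients never evaluated from patients evaluated and found negative.
- **Deaths.** A reader might infer that early deaths also distort the comparison, making the undiagnosed group look worse. The documents do not support this. A patient who dies in week 4 has no discharge or one-year scale score and drops out of the planned tests unless a score is assigned. The bias rests on early discharges alone. Those who leave in week 4 have no T1 imaging either, so the imaging comparison at T1 does not include them.
- **Timing.** A reader might infer that no patient can be diagnosed before day 47. That is too strong. The meeting is at about day 40, later reviews have no stated timing, and the confirmation criterion alone could be met at the assessment one day after the tap test (about day 41). What the text supports is that no confirmation is scheduled before about day 47.
- **Few may leave early.** For undiagnosed patients section 2.4 sets T2 at three months from admission and lists it before discharge. The authors thus seem to expect most stays to exceed three months. This is the strongest point, and it puts the likely bias at the low end. It does not remove dependence on stay altogether, since reviews continue during the stay and the introduction says diagnosis usually comes 3–12 months after injury.
- **Status of the claim.** Section 3 states an expectation, not a primary conclusion. That is so, but it is the reading this comparison is meant to inform.

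**Conclusion.** The point holds on mechanism. The diagnosed group is conditioned on a stay of about seven weeks, the undiagnosed group is not, and the stated tests do nothing about it. The direction, if early leavers are good recoverers, is a spurious disadvantage for patients with hydrocephalus.

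The size cannot be settled from the documents. Under the assumed ranges it runs from negligible (0.025 SD, 5.1% false rejection) to material (0.30 SD, 22–26% false rejection), against a standard error of 0.23–0.25 SD, and the visit schedule favours the low end. A claim that the comparison is seriously biased would go beyond the text. The supportable claim is that it is open to a bias of unknown size that a low-cost change to the analysis would largely remove.

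**What to change.** - **Main comparison.** Restrict it to patients still in hospital at completion of the first scheduled work-up, fixed in advance at about day 47. Patients judged not suspected at the first meeting should meet the same minimum stay. A landmark at the meeting itself would not do: patients leaving between days 40 and 47 would again default to undiagnosed.
- **Earlier exits.** Report the number and outcomes of those discharged or dead before the landmark as a separate unevaluated group.
- **Later diagnoses.** Show patients diagnosed at subsequent reviews separately, with a sensitivity analysis that reclassifies them. A time-varying exposure would not suit a single discharge score.
- **All-patient comparison.** Keep it as a secondary analysis, labelled with its limitation.

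The cost is wording. Section 2.5 already analyses length of stay and time from admission to diagnosis, so admission, discharge and diagnosis dates are needed anyway; the article does not say whether team evaluation dates are recorded, and this should be confirmed. The undiagnosed group becomes somewhat smaller, and the conclusion applies to patients staying at least about seven weeks. No change to clinical timing is implied.

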## 4. Discussion

Secondary hydrocephalus is a well-known complication of sABIs that may delay or negatively affect patients’ recovery, apparently resulting from multiple factors. Currently, there is no gold standard for its detection, but early diagnosis and treatment are fundamental to improve patients’ prognosis and rehabilitation outcomes [20,44]. In this paper, we have described the study protocol of a prospective cohort study that aims at validating a new clinical protocol for the diagnosis of secondary hydrocephalus. 

The liquor subtraction test is essential for the diagnosis [5,8,45]; however, because of its transient effect, a standardized and timely evaluation is mandatory.

Secondary hydrocephalus is under-diagnosed and less studied compared to idiopathic normal-pressure hydrocephalus (iNPH). In a recent retrospective study, Lalou et al. [44] found that resistance to CSF outflow and the pulse amplitude of intracranial pressure were significantly lower in PTH compared to iNPH and did not always reflect the degree of hydrocephalus or atrophy reported on CT/MRI. More studies on CSF dynamics are needed in order to assess the CSF circulation between people with trauma or hemorrhage compared with people with iNPH. 

Wu and colleagues [46] described secondary low-pressure hydrocephalus (LPH) and negative-pressure hydrocephalus (NegPH) that have been rarely reported and insufficiently recognized pathophysiologically. They suggested that, although the current classifications of hydrocephalus fail to provide clinical guidance to manage LPH and NegPH properly, they offer a new therapeutic viewpoint in order to recover the ventricular enlargement back to a normal size as far as possible from hydrocephalus with ventriculomegaly, regardless of the ventricular pressure. 

Given these premises, we plan to systematically submit all patients with sABIs to a timely and structured protocol that includes a clinical assessment, tap test, CSF examination, and neurophysiological and neuroradiological exams. In our protocol, neuroimaging is performed according to the timing based on the literature and our experience, in order to capture the hydrocephalus as soon as possible. 

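### The undiagnosed comparator in the prospective cohort includes suspected, tap-negative patients, so this contrast alone cannot support a claim of similarity to patients free of hydrocephalus

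*Protocol article*

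**What the plan says.** Section 2.4 sets out a two-step pathway. The multidisciplinary team will "identify patients with suspected hydrocephalus based on the presence of at least one of the following criteria". One route is radiological. The other is clinical: "Clinical criteria: worsening or stopping of clinical recovery as assessed based on clinical scales and functional tests". Suspected patients then have a tap test, and "the diagnosis will be confirmed when at least one of the following changes occurs after TT". The listed changes are improvements in the DRS, the LCF, certain CRS-R items or a functional test.

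Section 2.5 then analyses the prospective cohort in two groups: "The same tests will be used to compare patients with and patients without a diagnosis of hydrocephalus belonging to the prospective cohort". The outcomes include DRS, LCF and CRS-R scores at T3 and T4. Multivariable adjustment is described for the historical-versus-prospective comparison only.

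Section 3 gives the intended reading of this contrast: the protocol will "allow patients with hydrocephalus to obtain similar clinical rehabilitative outcomes and perceived quality of life to those who do not develop this complication".

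**The concern.** The pathway produces three kinds of patient: confirmed, suspected but tap-negative, and never suspected. The analysis has two groups. Tap-negative patients enter the undiagnosed group by elimination, because a diagnosis requires improvement after the tap test.

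The article gives its own reasons not to treat every tap-negative patient as free of hydrocephalus. The Introduction says that there is no reference standard, that atrophy and fluid accumulation can be hard to tell apart, and that earlier cases may have gone undetected. The Discussion says that the effect of fluid removal is transient.

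Patients suspected on the clinical criterion were also picked out because their recovery had stalled or reversed on clinical scales, and the DRS, LCF and CRS-R are also the outcomes. If they do worse, the comparator looks worse and confirmed patients look closer to it. The expected finding is similarity, so this error would be read as success.

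**Working it through.** **1. The plan's own figures.** Section 2.2 gives two years at 50–60 patients a year and about 20% with hydrocephalus.
- Total: 2 × 50 = 100 to 2 × 60 = 120, as stated.
- Confirmed: 0.20 × 100 = 20 to 0.20 × 120 = 24, consistent with the stated minimum of 20.
- Undiagnosed: 100 − 20 = 80 to 120 − 24 = 96.

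**2. Shift in the comparator.** Let r be the number suspected per confirmed case, f the tap-negative share of the undiagnosed group, and g the deficit of tap-negative against never-suspected patients in SD units (positive = worse). Then:
- f = (r − 1) × confirmed / undiagnosed = (r − 1) × 20/80 = (r − 1) × 0.25; 24/96 gives the same factor.
- Shift towards worse outcomes = f × g.

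The article gives neither r nor g, so both are assumptions.

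| r (assumed) | Tap-negative among 80–96 | f | Shift, g = 0 | Shift, g = 0.5 | Shift, g = 1.0 |
|---|---|---|---|---|---|
| 1.25 | 5–6 | 0.0625 | 0 | 0.03 SD | 0.06 SD |
| 1.5 | 10–12 | 0.125 | 0 | 0.06 SD | 0.13 SD |
| 2 | 20–24 | 0.25 | 0 | 0.13 SD | 0.25 SD |
| 3 | 40–48 | 0.50 | 0 | 0.25 SD | 0.50 SD |

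The top of the range needs 60 of 100 patients to be suspected and a full 1 SD deficit. If g were negative, the shift would reverse. A worse comparator means a higher mean DRS but a lower mean LCF or CRS-R.

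**3. Effect on the contrast.** Suppose confirmed patients truly do 0.5 SD worse than never-suspected patients, and r = 2, so f = 0.25. The observed gap is 0.5 − f × g. Power is two-sided at 0.05 by normal approximation, with the SD inflated for mixing.
- g = 0.5: gap 0.5 − 0.125 = 0.375 SD; power 0.31 (20 vs 80) to 0.36 (24 vs 96).
- g = 1.0: gap 0.5 − 0.25 = 0.25 SD; power 0.15 to 0.17.
- Confirmed versus never suspected only: gap 0.5 SD; power 0.49 (20 vs 60) to 0.56 (24 vs 72).

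**4. Precision.** The standard error in SD units is √(1/n₁ + 1/n₂).
- 20 vs 80: 0.250, so the 95% half-width is 1.96 × 0.250 = 0.49 SD. For 24 vs 96 it is 0.45 SD.
- 20 vs 60: 0.258, half-width 0.51 SD. For 24 vs 72 it is 0.46 SD.

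Dropping the tap-negative group therefore costs little precision, because the confirmed group dominates the standard error. The 0.13–0.25 SD shift at r = 2 also lies inside the sampling uncertainty of the planned contrast, so the two-group result could not reveal it.

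**The case against.** The strongest objection is that the bias is not demonstrated. Suspicion needs only one criterion, which may be a single imaging sign with no clinical decline. A tap-negative patient whose ventricles are enlarged by atrophy does not have hydrocephalus and belongs in the comparator. The article gives no outcomes for these patients. Other features act on the confirmed group. Section 2.4 says "Both the severity of the clinical condition and the consent being denied by family are reasons that preclude the intervention", even after confirmation, so some severely affected, unshunted patients stay in the diagnosed group and push away from similarity. Defining diagnosis by tap response selects responders and pushes the other way. All this stands: neither size nor net direction can be settled.

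A second objection concerns the remedy. Suspicion is reassessed throughout the stay, on scales that overlap the outcomes. Never-suspected patients are therefore selected after baseline for continued recovery, and using them alone would favour the comparator. This also stands, and it rules out simply replacing the planned group.

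Third, this is not the historical comparison that tests the main aims, Figure 2 is not available here, and a fuller document may define strata. That limits the weight of the point. However, Section 2.5 itself fixes a two-group contrast, and Section 3 fixes a reading that this contrast does not match.

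A reader might infer two further things that the text does not support:
- **An untapped subgroup in the comparator.** Section 2.4 says suspected patients "will undergo further evaluations to confirm the diagnosis, specifically:High-volume tap test (TT"), so an untapped suspected patient would be a deviation, not a planned category.
- **A conflict with the Discussion**, which plans to "systematically submit all patients with sABIs to a timely and structured protocol that includes a clinical assessment, tap test". Section 2.4 describes the same protocol with the tap test as its conditional step, so the passages are compatible.

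**Conclusion.** The point holds in a limited form. By the article's own definitions, the undiagnosed group contains suspected, tap-negative patients. It is therefore not cleanly the population named in the expected conclusion, and no adjustment is stated for this contrast. Mixing could draw the result towards the expected similarity. The shift is 0 to 0.50 SD for r between 1.25 and 3 and g between 0 and 1.0, all assumed.

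The article does not support the stronger claim that the comparator is definitely made worse, or that the net bias must favour the expected finding. A positive g is plausible for patients flagged on the clinical criterion, but it is nowhere stated.

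The features that act on the confirmed group are common to both contrasts. They leave the net direction of either one open, but they do not explain a difference between the two. Setting the contrasts side by side is therefore informative even though neither is unbiased.

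**What to change.** - Keep the planned contrast of diagnosed versus undiagnosed patients.
- Report T3 and T4 outcomes for three groups: confirmed; suspected and tap-negative; never suspected. Assign each patient by final status at the end of the inpatient stay, because suspicion can arise later and a tap-negative patient may be re-evaluated.
- Add a sensitivity contrast of confirmed versus never suspected, with its effect size and confidence interval beside those of the planned contrast.
- Claim similarity to patients without the complication only if both contrasts agree. If they differ, limit the statement to patients without a confirmed diagnosis and show the middle group's results.

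**Cost.** The change is to analysis wording, since suspicion status and tap results already arise from the pathway. The reference group shrinks in the sensitivity analysis, for example from 80 to about 60 if 40 of 100 are suspected, and the 95% half-width widens from 0.49 to 0.51 SD. The never-suspected group is itself selected for good recovery, so it should stand beside the planned comparator and not replace it.
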